## 3. Measurement

### Statistical Analyses

All the analyses will be carried out using SPSS version 14.0 for Windows (SPSS Inc., Chicago, IL, USA, 2005).

Improvements in psychosocial functioning and cognitive performance will be assessed using effect size estimates obtained from within- and between-group differences at repeated measures analyses of variance (rm-ANOVAs). In case of attrition rate > 20%, a mixed model will be employed, under the missing at random (MAR) assumption. Regarding clinical symptoms, treatment effects will be compared among patients with and without residual symptoms (≥1 on Y-MRS, ≥3 on HAM-D) using t-tests.

Given the small sample size, the investigation of potential predictors of response through regression analyses should be considered largely explanatory. However, some regression analyses will be performed as deemed important in light of the feasibility nature of this trial; variables of interest will include participants’ age, duration of illness, baseline functioning, baseline cognitive performance and change in cognitive performance as well as potentially emerging predictors of dropout. In fact, participants leaving the study early will be compared with those completing all study procedures in terms of demographic and clinical variables using inferential statistics to assess potential moderators.

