### Trial Aims and Objectives

The present project aims to evaluate the efficacy of FR in improving psychosocial functioning, cognitive deficits and the quality of life in a sample of euthymic patients diagnosed with BD. This intervention will be compared with a control condition: a group of participants will follow a treatment as usual (TAU) program that includes only pharmacological treatment according to good clinical practice.

The primary objective measure is the score on the Functioning Assessment Short Test (FAST) from the baseline to the endpoint. The hypothesis is that an integrated treatment (FR + TAU) may be more effective than the standard treatment (TAU) in improving psychosocial functioning in BD. We hypothesize that patients involved in an FR group will show improvements in overall psychosocial functioning compared to patients included in the control group (TAU).

One secondary objective is to evaluate whether integrated treatment (FR + TAU) can allow a more effective response in improving neurocognitive and socio-cognitive performance and subthreshold affective symptoms compared to standard treatment (TAU). A further secondary objective is the identification of possible sociodemographic, clinical, cognitive and functional predictors of clinical, cognitive and functional responses in the two groups of patients.

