#### 2.3.1. Inclusion Criteria

Eligible participants will be fully informed about the study procedure and included only if providing written informed consent. They will be required to meet the following inclusion criteria: (a) age between 18 and 55 years; (b) education level of ≥8 years; (c) diagnosis of BD type I or II as referred from treating psychiatrist and confirmed at recruitment using the Structured Clinical Interview for Disorder for DSM-5, Clinical Version (SCID-5-CV) [52]; (d) clinical re0mission according to DSM-5 criteria (no mood episodes for ≥2 months) [53]; (e) euthymic phase at baseline assessment (defined as scoring both ≤6 points on the Young Mania Rating Scale (Y-MRS) [54] and ≤8 points on the Hamilton Depression Rating Scale (HAM-D)) [55]; (f) moderate to severe degree of functional impairment (defined as a score of ≥18 points on the Functioning Assessment Short Test (FAST)) [56]; (g) adequate mastery of Italian language, spoken and written.

According to these criteria, participants will not be pre-screened for neurocognitive impairment since the main focus of FR is functioning rather than cognition, and this program is primarily (though not exclusively) aimed at promoting psychosocial functioning among patients with significant impairment in occupational and interpersonal domains [15].

Concomitant medications will be kept stable as much as possible throughout the trial in order to reduce confounding effects. For patients receiving lithium therapy, the serum dose will be monitored over time and maintained within the therapeutic range. No major restrictions will be applied in terms of medication doses or compounds in order to not affect trial feasibility and the generalizability of the results; however, subsequent analyses are going to include the investigation of the potential influence of these parameters on treatment effect.

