#### 2.4.2. Allocation and Blinding

Patients fulfilling all inclusion criteria will be randomized to the two parallel groups by a researcher not involved in the subsequent trial procedures, using a computer-based system (1:1 ratio). The allocation sequence will not be based on any stratification procedure, and all the details related to randomization will be kept locked following treatment allocation (Figure 1).

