### 2.6. Assessment Phase

Outcomes will be evaluated at baseline (T0), at the end of active treatment phase (T1) and 6 months thereafter (T2), using standardized and previously validated rating instruments based on Italian normative data. Assessments will be conducted by two trained residents in psychiatry, with at least 1 year of experience, not involved in treatment delivery for this trial and blinded to study treatment condition. Inter-rater reliability will be verified before study start. Patients will be instructed not to reveal information on their therapy during assessments. Eventual cases of blinding violations will be reported. Effectiveness of blinding will be verified at the end of the trial, asking assessors to guess which group the patients belong to and then verifying the answers using the McNemar test of independence [58]. Assessment at T1 is meant to obtain effectiveness data, together with essential information on trial and intervention feasibility. A follow-up observation will be performed to verify the long-term persistence of effects and their translation to everyday functioning, which is hypothesized to consolidate over time [59,60] (Figure 2).

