#### Power—Sample Size Calculation

The required sample size was estimated based on power calculations performed on the software G*Power [65] and assuming an effect size of 0.25 on the ANOVA group × time interaction for the primary outcome (psychosocial functioning measured with the FAST scale). This effect size is in line with that observed in previous studies adopting similar procedures and intervention paradigm [39]. With alpha at 0.05, the effect size could be detected with 95% power when enrolling a sample of 44 participants (22 per group). Assuming 20% attrition, it was decided to set the recruitment target at 54 participants (27 per group).

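### Improvement is to be judged partly on within-arm change in patients selected for a high FAST score, and no single visit and between-arm contrast is fixed as primary

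*Protocol article*

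**What the plan says.** All places are in the protocol article.

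- **Statistical Analyses.** Improvement in functioning and cognition is to be "assessed using effect size estimates obtained from within- and between-group differences at repeated measures analyses of variance (rm-ANOVAs". The two kinds of difference stand side by side. Neither is called primary or descriptive, and no visit is named.
- **2.3.1 Inclusion Criteria.** Patients must have a "moderate to severe degree of functional impairment", defined as FAST ≥18. Section 2.7 makes FAST the primary outcome.
- **Trial Aims and Objectives.** "The primary objective measure is the score on the Functioning Assessment Short Test (FAST) from the baseline to the endpoint". The endpoint is not defined further. The hypothesis in the same section compares FR + TAU with TAU alone.
- **2.6 Assessment Phase.** There are three visits: T0, T1 (end of treatment) and T2 (six months later). "Assessment at T1 is meant to obtain effectiveness data", while follow-up is to check persistence.
- **Power—Sample Size Calculation.** The trial is sized "assuming an effect size of 0.25 on the ANOVA group × time interaction for the primary outcome". "With alpha at 0.05, the effect size could be detected with 95% power when enrolling a sample of 44 participants (22 per group".

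**The concern.** Patients enter because their FAST score is high on the day it is measured. Part of that excess is chance, so the mean falls on retest in both arms even if nothing works. A within-arm effect size counts this fall as benefit, along with any other change over time that both arms share. Only the difference between arms removes it.

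The comparison itself is described in different ways. The aims speak of change from baseline to an undefined endpoint, the analysis section of within- and between-group effect sizes, and the power section of a group × time interaction. At stake are two choices left open until the data are seen: how much weight the FR arm's own change receives, and whether T1, T2 or the overall interaction is presented as the main result.

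**Working it through.** **1. The plan's own sample size.** From the power section: f = 0.25, alpha 0.05, 95% power, two groups. From section 2.6: m = 3 measurements. Assumed, because not stated: correlation between visits ρ = 0.5 and sphericity.

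λ = f²·N·m/(1 − ρ) = 0.0625 × 44 × 3 / 0.5 = 16.5, with df = (2 − 1)(3 − 1) = 2 and (44 − 2)(3 − 1) = 84. Power is 95.6%. At N = 42, λ = 15.75 and power is 94.6%. So 44 is reproduced.

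With m = 2 and ρ = 0.5, λ = 11 on 1 and 42 df. Power is then 90.0%, and 54 completers are needed for 95%. The match is not unique: at m = 2 the required N is 54 for ρ = 0.5 and 34 for ρ = 0.7, so some value in between would also give 44. At m = 3 it is 60 for ρ = 0.3 and 28 for ρ = 0.7. The three-visit interaction is the reading that fits the visit schedule.

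**2. What that interaction can show.** Let the FR − TAU difference at T0, T1 and T2, in SD units, be d_t with mean d̄. Then λ = (N/4)·Σ(d_t − d̄)²/(1 − ρ). For each of the patterns (0, δ, δ), (0, δ, 0) and (0, 0, δ), the sum is 2δ²/3. At N = 44 and ρ = 0.5, λ = 11 × (2/3)δ²/0.5 = 14.67δ². With δ = 0.8, λ = 9.39 and power is about 77% for all three patterns. Reversing the sign of δ changes nothing. A significant result therefore does not say at which visit the arms differ, or in which direction. Setting λ = 16.5 gives δ = √(16.5/14.67) = 1.06 SD, which is the design effect under an equal difference at T1 and T2.

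**3. Regression to the mean within an arm.** Assumed, with no figures in the document: a normal source population with FAST mean μ = 20–30, SD 12 and retest correlation r = 0.6–0.8, and the qualifying score serving as baseline. With a = (18 − μ)/12 and h = φ(a)/(1 − Φ(a)), the untreated fall is (1 − r)·h·12.

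| μ | a | h | fall, r = 0.6 | fall, r = 0.8 |
|---|---|---|---|---|
| 20 | −0.167 | 0.3934/0.5662 = 0.695 | 3.34 | 1.67 |
| 30 | −1.000 | 0.2420/0.8413 = 0.288 | 1.38 | 0.69 |

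The SD of change is √[(1 − r)²·V + 144(1 − r²)], with V = 144(1 + a·h − h²). On that basis, a paired test in one arm of 27 would show significant improvement in about 7% to 38% of trials with no treatment effect, against a nominal 2.5% in that tail. The expected fall is the same in both randomised arms, so its contribution to the between-arm difference is zero.

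**4. Baseline adjustment against the planned interaction.** For FAST at one visit adjusted for baseline, the residual SD is √(1 − ρ²) = √0.75 = 0.866. The noncentrality is (δ/0.866)·√(22/2) on 41 df. The comparator is the 2-df interaction of step 2 with an equal effect at T1 and T2.

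| δ (SD) | interaction λ | interaction power | adjusted noncentrality | adjusted power |
|---|---|---|---|---|
| 0.6 | 5.28 | 51% | 2.30 | 61% |
| 0.8 | 9.39 | 77% | 3.06 | 85% |
| 1.06 | 16.5 | 95.6% | 4.06 | 97.7% |

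The gain depends on ρ. At δ = 0.8 the same formulas give 62% to 78% for ρ = 0.3, and 94.5% to 95.2% for ρ = 0.7. This ρ refers to enrolled patients. It is not the r of step 3, which refers to the unselected source population.

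**The case against.** A reader might infer that regression to the mean will be counted as efficacy, or that the trial has no comparative primary test at all. The document does not support either reading. The hypothesis is stated against TAU, and the sample size rests on the group × time interaction for FAST. Selection at FAST ≥18 affects both arms equally in expectation, so that interaction is unbiased. Reporting within- and between-group terms from a repeated-measures ANOVA is routine, and the analysis section nowhere says that within-arm change would suffice for a claim. All of this stands.

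The visit is also less open than the aims section alone suggests, because section 2.6 gives T1 the effectiveness role and T2 the persistence role. That narrows the choice but does not close it: no section calls T1 primary, and the interaction used for sizing spans all three visits.

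It is tempting to call the lack of baseline adjustment an error, or to quote a gain from 74% to 85% at 0.8 SD. That figure takes a two-visit change score as the comparator, which does not match the plan's stated sizing. Against the three-visit interaction the gain is about 8 percentage points at 0.8 SD and about 2 at the design effect. The interaction is a legitimate choice.

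Finally, a condensed article may leave detail to a fuller plan. But naming within-group differences as a basis for judging improvement is something this text states, not something it omits.

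**Conclusion.** The point holds in limited form. The analysis section should not rest improvement on within-arm effect sizes in patients selected on the outcome scale. The artefact is about 0.7 to 3.3 FAST points per arm under the assumed mean, SD and retest correlation. Its direction is firm for any retest correlation below 1, while its size is illustrative. It affects within-arm change and the main effect of time, not the randomised comparison.

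The primary contrast is indicated but not fixed. T1 is implied, the endpoint is undefined, and the stated N fits an omnibus test that identifies neither visit nor direction (assuming three measurements and ρ = 0.5). Baseline adjustment is an improvement available from data already collected, and its value depends on ρ. None of this invalidates the design. It is a matter of stating the analysis so that the result cannot be chosen afterwards.

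**What to change.** - State one primary analysis: the FR − TAU difference in FAST at T1, adjusted for baseline FAST, with a 95% confidence interval and a two-sided test at 0.05. Define the endpoint in the aims section as T1.
- Make the T2 difference and the group × time interaction secondary.
- Report within-group changes descriptively only, and remove them as a basis for judging improvement.
- Use the same form for BAC-A as a secondary outcome.
- Restate the power section for the new contrast, giving the assumed effect in SD units and ρ. The present 95% statement belongs to a different test and does not carry over.

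No new data are needed, since baseline FAST is already collected. The costs are that T2 loses any claim to primary status and that the power paragraph must be derived again. At 44 completers and ρ = 0.5, the new contrast has 97.7% power at 1.06 SD, 85% at 0.8 SD and 61% at 0.6 SD.

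### The mixed model is held back until attrition exceeds 20%, the planned rate, so one dropout can decide the primary FAST model and patients seen at T0 and T1 only may be discarded

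*Protocol article*

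**What the plan says.** FAST is the primary outcome (section 2.7), measured three times: "Outcomes will be evaluated at baseline (T0), at the end of active treatment phase (T1) and 6 months thereafter (T2". Section 2.6 adds that T1 is the visit meant to supply the effectiveness data, with T2 testing whether effects persist.

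Under Statistical Analyses, functioning and cognition are assessed from "within- and between-group differences at repeated measures analyses of variance (rm-ANOVAs". The same paragraph sets the exception: "In case of attrition rate > 20%, a mixed model will be employed, under the missing at random (MAR) assumption". It describes no imputation or other handling of incomplete records for the rm-ANOVA.

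The Sample Size Calculation powers the group by time interaction ("assuming an effect size of 0.25 on the ANOVA group × time interaction for the primary outcome") and arrives at 44 patients: "With alpha at 0.05, the effect size could be detected with 95% power when enrolling a sample of 44 participants (22 per group". It then allows for loss: "Assuming 20% attrition, it was decided to set the recruitment target at 54 participants (27 per group".

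Section 2.7 counts as dropout the withdrawal of consent, a mood episode or a major drug change made to avert one, interruption of drug therapy, and a run of missed FR sessions.

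**The concern.** A classical rm-ANOVA with three occasions needs all three scores from each patient. Someone assessed at T0 and T1 but lost before T2 contributes nothing, even to the T1 comparison. A likelihood-based mixed model keeps that patient and is valid under MAR whether 5% or 30% are lost. Nothing changes statistically at 20%.

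The trigger also sits exactly on the attrition that the trial was sized for. Which of two models is primary, and which patients are in it, therefore depends on a dropout or two around the planned rate. At stake are the precision of the T1 comparison and protection against bias if the patients who leave differ between arms in their earlier FAST scores.

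**Working it through.** **1. The plan's own sample size.** Inputs from the article: f = 0.25 (read as Cohen's f), two groups, three visits, alpha 0.05, N = 44. Assumed because not stated: correlation between visits ρ = 0.5 and sphericity.

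- Noncentrality λ = f² × N × m / (1 − ρ) = 0.0625 × 44 × 3 / 0.5 = 16.5
- df1 = (2 − 1)(3 − 1) = 2; df2 = (44 − 2)(3 − 1) = 84
- Power = 95.6%, so 44 reproduces.

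Inflation: 44 / (1 − 0.20) = 55, against the stated 54. This is close enough and is not at issue. The step from 54 to 44 counts only completers, which fits a complete-case rm-ANOVA.

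**2. Where the switch falls.**

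| Dropouts of 54 | Attrition | Primary model | Completers | Power on completers (ρ = 0.5) |
|---|---|---|---|---|
| 10 | 10/54 = 18.5% | rm-ANOVA | 44 | 95.6% |
| 11 | 11/54 = 20.4% | mixed model | 43 | 95.1% |

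Exactly 20% of 54 is 10.8 patients, so the threshold lies between two adjacent counts.

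**3. How often each model is used.** With dropouts X ~ Binomial(54, p), P(rm-ANOVA) = P(X ≤ 10):

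- p = 0.15: 0.82
- p = 0.20: 0.47
- p = 0.25: 0.17

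**4. Precision at T1.** Suppose 27 per arm, ρ = 0.5, and 5 per arm (18.5%) missing T2 only, at random. The SD of the T0–T1 change is √(2 − 2 × 0.5) = 1 in units of the FAST SD. For a true difference d in change, the two-sample t-test has noncentrality d × √(n/2), with n per arm.

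| d (assumed) | All T1 data, n = 27 | Listwise, n = 22 |
|---|---|---|
| 0.8 SD | 0.8 × √13.5 = 2.94; power 82% | 0.8 × √11 = 2.65; power 74% |
| 0.6 SD | 0.6 × √13.5 = 2.20; power 58% | 0.6 × √11 = 1.99; power 49% |

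**5. Bias.** Same layout, no true effect, 20,000 simulated trials per scenario. The 5 patients lost per arm are those with the highest value of s × T1 score + N(0,1), with s = 1 or 2 where dropout depends on T1.

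| Dropout after T1 | Listwise bias, T0–T1 contrast | Listwise type I error | All T1 data |
|---|---|---|---|
| FR: depends on poor T1 FAST; TAU: random | 0.11 to 0.14 SD in favour of FR | 6.3 to 7.9% | 0.00 SD, about 5% |
| Same dependence in both arms | about 0.00 SD | 5.4 to 5.7% | about 0.00 SD, about 5% |

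A second large-sample illustration used a true effect of −0.50 SD, with dropout depending on earlier scores both before and after T1. Equal 20% dropout in both arms left the complete-case change difference at −0.50 at T1 and T2. With all dropout in FR (about 39% there, 20% overall), it was −0.42 at T2, and completers differed at baseline by −0.27 SD. Bias therefore needs a difference between arms, and it can run in either direction.

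**The case against.** The strongest defence is that the rule is written in advance, names its threshold and its assumption, and depends on a count of dropouts rather than on FAST results. A reader might infer that the model is chosen after seeing the data. The text does not support that: the analyst has no discretion, and no type I error inflation from the switch itself has been shown.

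A reader might also infer that the trial will be underpowered. It was sized on 44 analysable patients, and 10 dropouts from 54 leave 44. The losses in step 4 concern a two-visit contrast with assumed effects, not the interaction test used for the sample size.

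Nor is complete-case analysis unbiased only when data are missing completely at random. With the same mechanism in both arms, the treatment contrast was essentially unbiased. The one dropout criterion specific to FR, missed sessions, acts during the intervention and so before T1. The asymmetric loss after T1 in step 5 is an assumption that this criterion does not establish. The other criteria apply to both arms.

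Finally, the article never uses the term complete-case, is a condensed account, and describes a pilot. Listwise loss is inferred from the named method, the absence of stated imputation and the sizing on completers.

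All of this lowers the severity. None of it supplies a reason to withhold the mixed model at 20% attrition or below. The article states the trigger outright, so it is a choice already made rather than a detail left to another document.

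**Conclusion.** The concern holds as a weakness that should be fixed; it does not invalidate the plan. The 20% trigger has no statistical basis and coincides with the planned attrition, so the primary model turns on one patient. At a 20% dropout probability the choice is close to a coin toss (0.47 for the rm-ANOVA). It would be too strong to say that the expected case falls under the rm-ANOVA, because the mixed model is then slightly the more likely.

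The cost has two parts:

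- **Precision at T1.** The example of 82% to 74% rests on ρ = 0.5, a 0.8 SD effect and every dropout having a T1 score. The article does not say how many dropouts will have one.
- **Exposure to bias.** The 0.11 to 0.14 SD arises only if dropout related to earlier FAST differs between arms; it is about 0 otherwise.

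The stated sample size and power are unaffected.

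**What to change.** Delete the 20% trigger. State that the primary FAST analysis is a likelihood-based mixed model for repeated measures with arm, visit and arm by visit, unstructured covariance, and all available FAST scores, whatever the attrition. Model baseline as one of the repeated outcomes. If it enters only as a covariate, a patient with T0 alone has no outcome record and leaves the analysis, just as in the rm-ANOVA. Keeping such patients adds little information on the treatment effect, so the main gain is from those with T1 but not T2. Report the complete-case rm-ANOVA as a sensitivity analysis.

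The cost is a sentence or two. The plan already names a mixed model, and the change needs no further data and no change to the 54 patients. It should be made before unblinded outcome data are seen.

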Additional outcomes will be *evaluated as secondary endpoints:* (a) global neurocognitive performance measured with the Brief Assessment of Cognition in Affective Disorders (BAC-A), Italian version [61]. This scale has been derived from a neuropsychological battery commonly used to assess cognitive performance in people living with schizophrenia, the Brief Assessment of Cognition in Schizophrenia (BACS) [62], but is designed to be sensitive and specific in patients with affective disorders such as BD. It contains six tests that assess different cognitive domains (List Learning for Verbal Memory, Digit Sequencing Task for Working Memory, Token Motor Task for Motor Speed, Verbal Fluency Category Instances for Semantic Fluency and Controlled Oral Word Association Test for Letter Fluency, the Tower of London Test for Executive Functions and Symbol Coding for Attention and Motor Speed) that are contained in the BACS and features also an affective processing test [63]. The six core BACS measures can be standardized into z-scores according to available normative data [61], and a global cognition composite score can be calculated by averaging the scores of single scales. (b) Socio-cognitive performance measured with the Mayer–Salovey–Caruso Emotional Intelligence Test (MSCEIT), Italian version [63]: this test assesses emotional processing ability and includes a total of 141 items divided in 8 tasks. The score on these tasks can be combined into 4 sub-scales that can be further combined in 2 areas and with a total score measuring global emotional intelligence. (c) Manic symptoms severity measured with the Y-MRS [54], a scale composed of 11 items. Four core items are graded from 0 to 8 without odd scores, and seven items are graded from 0 to 4; each item has specific anchor points, and higher scores reflect more severe manic symptoms. (d) Depressive symptoms severity measured with the HAM-D [55], a scale composed of 17 items. Each item has specific anchor points; 8 items can be graded from 0 to 2 and 9 items can be graded from 0 to 4, with higher scores reflecting greater symptoms severity; a score ≤ 7 corresponds to the absence of depressive symptoms.

The number and patterns of dropouts will also be reported, along with descriptions of the rate of enrollment and consent of eligible subjects, the percentage of session attendance and the reasons for non-attendance.

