Patients will be considered dropouts in the following cases: (a) withdrawal of consent; (b) emergence of a full-blown mood episode and/or major change in drug therapy needed in order to prevent this eventuality within the study period; (c) discontinuation of drug therapy for ≥5 consecutive days; (d) missing ≥5 consecutive FR sessions.

Additional information will be collected regarding demographic and clinical characteristics of the included participants: age, sex, employment status, familiarity for psychiatric disorders, BD type I/II, cycling, seasonality, age at onset, duration of illness, number of previous episodes, history of psychosis, history of suicide attempts, presence of baseline residual symptoms and baseline cognitive performance (BAC-A), current therapy (baseline medications, changes in medication within the study period, lithium (yes/no), antipsychotics (yes/no)) and global daily drug burden, estimated using the WHO defined daily dose (DDD) method [64].

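### Dropout is defined by events that plausibly predict later FAST, one of them possible only in the FR arm, so an analysis resting on MAR or on complete cases alone can bias the FR effect

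*Protocol article*

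**What the plan says.** All places are in the protocol article; no separate analysis plan is shown.

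- **Analysis** (section 3, Statistical Analyses). The default is effect sizes from "within- and between-group differences at repeated measures analyses of variance (rm-ANOVAs"), with no handling of missing values stated. Above a threshold the method changes: "In case of attrition rate > 20%, a mixed model will be employed, under the missing at random (MAR) assumption".
- **Dropout** (section 2.7). Apart from a patient withdrawing consent (a), three kinds of event count. Rule (b) is "emergence of a full-blown mood episode and/or major change in drug therapy needed in order to prevent this eventuality within the study period". The next, rule (c), concerns a break in medication: "discontinuation of drug therapy for ≥5 consecutive days". The last, rule (d), concerns attendance: "missing ≥5 consecutive FR sessions".
- **Visits** (section 2.6). "Outcomes will be evaluated at baseline (T0), at the end of active treatment phase (T1) and 6 months thereafter (T2"). Section 2.3.1 requires euthymia at baseline, so every T0 FAST is a euthymic one.
- **Safeguards stated.** "The number and patterns of dropouts will also be reported" (section 2.7). Also, "participants leaving the study early will be compared with those completing all study procedures in terms of demographic and clinical variables" (Statistical Analyses). Session attendance, reasons for non-attendance and medication changes are recorded.

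The article does not say whether FAST is still rated at T1 and T2 once a patient counts as a dropout.

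**The concern.** MAR here requires that, given arm and the FAST scores already in the model, leaving carries no further information about the FAST scores that are missing. Relapse, stopping medication and not attending the programme plausibly do carry such information.

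A patient who leaves before T1 and is not rated again gives the model a single euthymic T0 score. The model then predicts that patient's T1 and T2 from patients in the same arm who stayed and had a similar T0. An FR patient who stopped attending is credited with the FR completers' expected course, and a relapsed patient in either arm with the course of patients who did not relapse.

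Rule (d) makes this unequal between arms. Only FR patients have sessions to miss, and sessions take place only during active treatment, so a patient who leaves under (d) always does so before T1. Rules (b) and (c) can operate in both arms and also during follow-up.

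At stake is the primary FAST contrast. The article wants evidence of effectiveness in clinical settings (Background) and foresees that the results could support inclusion in treatment recommendations (Discussion).

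**Working it through.** **1. The plan's own figures.** For the group × time interaction in a repeated-measures ANOVA, λ = f²·N·m/(1−ρ), df1 = (k−1)(m−1) and df2 = (N−k)(m−1). With the stated f = 0.25, alpha 0.05, k = 2 and m = 3 visits, and with ρ = 0.5 and sphericity assumed, N = 44 gives power 0.956. This reproduces the stated 44 and 95%. Inflating for 20% attrition gives 44/0.8 = 55, against 54 stated.

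**2. Where the analysis switches.** Of 54 patients, 10 leavers are 18.5% (ANOVA) and 11 are 20.4% (mixed model). The expected attrition therefore lies on the threshold, and both analyses have to be considered.

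**3. Bias formula.** Let gain be the fall in FAST, and let d be the share of an arm that leaves with T0 only. If leaving is unrelated to T0 FAST, a MAR model recovers the completers' contrast, so

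bias = d_FR × (completer gain − leaver gain in FR) − d_TAU × (completer gain − leaver gain in TAU).

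**4. Inputs.** The article gives no arm-specific attrition and no leaver outcomes, so every input below is assumed: FR completers gain 6 points, TAU completers gain 0, and all leavers go before T1 and are not rated again. The estimate is then 6.0 throughout.

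| Leaving FR / TAU | Leaver gain FR / TAU | Bias | Estimate vs all randomised |
|---|---|---|---|
| 30% / 15% | 0 / 0 | 0.30×6 − 0.15×0 = +1.8 | 6.0 vs 4.2 |
| 30% / 15% | −5 / −5 | 0.30×11 − 0.15×5 = +2.55 | 6.0 vs 3.45 |
| 25% / 25% | 0 / −6 | 0.25×6 − 0.25×6 = 0 | 6.0 vs 6.0 |
| 15% / 35% | 0 / −6 | 0.15×6 − 0.35×6 = −1.2 | 6.0 vs 7.2 |
| 20% / 20% | 0 / 0 | 0.20×6 − 0.20×0 = +1.2 | 6.0 vs 4.8 |

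The first four rows have 22.5% or 25% attrition overall and would trigger the mixed model. The last is exactly 20%, so the ANOVA would be used.

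**5. Simulation check.** This used 27 per arm, 3,000 runs, an 8-point completer gain, SD 10, retest correlation 0.5 and leaving unrelated to T0. The baseline-adjusted MAR estimate against the truth was:

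- 25%/25%, leaver gain 0/0: 8.0 vs 6.0
- 35%/15%, leaver gain 0/0: 8.0 vs 5.2
- 25%/25%, leaver gain 0/−8: 8.0 vs 8.0
- 15%/35%, leaver gain 0/−8: 8.1 vs 9.6

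A completers-only change analysis gave about the same estimates in each case (8.0, 8.0, 8.0 and 8.1). Under these conditions the risk does not depend on which side of the 20% threshold the trial falls.

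**6. Milder inputs.** In the first row of the table, if FR leavers keep half the gain the bias is 0.30×3 = 0.9. If only half of the FR leavers go before T1, the bias in the T1 contrast is 0.15×6 = 0.9.

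**The case against.** **The article is a condensed document.** Sensitivity analyses to MAR are commonly left to a full protocol or analysis plan, so their absence alone is no finding. That stands. What remains is that two stated parts, the dropout definition and the missing-data assumption, fit together badly and unequally between arms.

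**Overstatement is not a consequence of the text.** A reader might infer that the model necessarily favours FR. It does not: rules (b) and (c) also apply to TAU, and MAR credits TAU leavers with the TAU completers' course. The zero and negative rows above show the result. Rule (d) makes overstatement a plausible risk, no more.

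**The events are observed.** A reader might infer that patients leave for unobserved reasons, which would contradict MAR outright. The rules can be applied only if the events are seen, and the article records them. What may be unobserved is the later FAST. Since the events are not stated to enter the model, MAR is doubtful, but it is not refuted.

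**The inputs lean towards the worst case.** Nothing says that rating stops at dropout, those who leave after T1 contribute a T1 score, and missing 5 of 21 sessions in a row is compatible with attending up to 16. All of this stands and reduces the size. Against it, the article contrasts early leavers with those who complete all procedures and raises recruitment from 44 to 54 for attrition. Both suggest that dropouts are treated as lost data.

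**The planned leaver–completer comparison.** It is meant to explore moderators, and it cannot test MAR, which concerns FAST scores nobody has seen. With 11 leavers against 43 completers it has 80% power only for differences of about 0.96 SD.

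**Aim and scale.** The article speaks of efficacy as well as effectiveness, and this is a pilot with about five leavers expected per arm (0.2 × 27 = 5.4). This argues for a light remedy.

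**Conclusion.** The concern holds as a risk that the stated rules create. If FAST is not rated after events (b) to (d), MAR given arm and earlier FAST is doubtful and asymmetric, and both the mixed model and a complete-case ANOVA inherit the problem.

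Under the assumed 6-point completer gain, no leaver gain, and 30% of FR and 15% of TAU patients leaving before T1, the estimate is 6.0 against 4.2, which is 43% too large (6.0/4.2 = 1.43). Other assumed inputs give anything from 6.0 against 3.45 to 6.0 against 7.2. The documents fix neither the direction nor the size, so the claim that the plan will overstate the FR effect is not supported. Nor does the point call for abandoning MAR as the main assumption, or question the clinical content of the dropout rules. It is an inexpensive improvement to the primary analysis.

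**What to change.** In Statistical Analyses:

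1. Keep the MAR mixed model as the main estimate, fitted to all randomised patients and using any FAST collected at the scheduled T1 and T2 after events (b) to (d). Say whether FAST is collected after these events.
2. At any attrition level, report beside it the FR–TAU difference with its 95% confidence interval from two sensitivity analyses:
   - jump to reference, with missing FR FAST following the TAU mean;
   - a delta adjustment in both arms over a range stated in advance, varied separately by arm, because the direction depends on TAU leavers as well.
3. State whether the conclusion survives both.

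The two analyses do different work. In the first row of the table, jump to reference returns 0.70×6 = 4.2, the all-randomised value. In the second it also gives 4.2, and a 5-point delta in both arms then gives 4.2 − 0.30×5 + 0.15×5 = 3.45.

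The cost is a few sentences and a few hours of analysis, with no extra patients or visits. The downside is that the reported effect may be smaller or less precise.
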